The primary objective of this study is to determine the effect of a 12-week dietary intervention with 8 g/day of prebiotic intake compared to placebo on glycemic control as measured by HbA1c in children diagnosed with DM1 for at least one year. The secondary objective is to determine the gut microbiota composition in children diagnosed with DM1 consuming prebiotic versus placebo. Further, we aim to examine the differences in gut permeability, serum inflammatory markers, glucagon-like peptide 1 (GLP-1) and GLP-2 and C-peptide in children diagnosed with DM1 consuming prebiotics versus placebo and to assess for diabetes-related adverse reactions (i.e. severe hypoglycemia and diabetic ketoacidosis) associated with use of prebiotics in children with DM1.

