### Randomization

Participants will be randomized via computer-generated numbers to intervention or placebo control in a 1:1 ratio. The intervention and placebo groups will not be matched (e.g. age, duration of T1DM, etc.). An investigator not involved in running the study will prepare the randomization sequences and have the random allocation sequence in numbered envelopes in a secure location that will be opened only once a participant has consented and enrolled in the study. The participants, trial coordinator and research staff who enroll the patients will remain blinded to the participants’ group assignment. Participants will be asked at the end of the study to which group they believed they were assigned.

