#### Glycemic control, inflammatory markers, GLP-1 and GLP-2

Blood will be collected at baseline, 3 months and 6 months for serum C-peptide, HbA1c, serum inflammatory markers (IL-6, IFN-gamma, TNF-alpha and IL-10), GLP-1 and GLP-2. Serum will be sent to Calgary Laboratory Services (Calgary, AB, Canada) for measurement of HbA1c by turbidimetric inhibition immunoassay (Roche Integra 800 CTS, Basel, Switzerland) and serum C-peptide by chemiluminescent assay (Siemens Immulite 2000, Erlangen, Germany). Serum inflammatory markers will be analysed by Milliplex Human Cytokine Magnetic Bead Multiplex kits (Millipore, St. Charles, MO, USA). GLP-1 and GLP-2 will be measured with ELISA kits (Millipore, St. Charles, MO, USA).

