
### Sample size

#### Internal pilot

The initial pilot study will aim to test the feasibility of a fully powered studied in children with type 1 diabetes. To test feasibility in this pilot study, we will enroll 15 subjects per arm. If we assume a drop-out rate of 20 % (12 subjects completing the study in each arm), power of 80 %, and alpha of 0.05 and a standard deviation of 1.3 for HbA1c, then with the pilot study we would be able to detect a mean difference in the absolute HbA1c of 1.5 between the placebo and prebiotic groups.

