### Analysis

Analysis will be performed using SPSS 22.0 software (IBM, New York, USA). Results will be considered statistically significant if *p* ≤ 0.05. Baseline descriptive data between the control and intervention group will be compared using chi-square for categorical variables and *t* tests for continuous variables. The primary outcome of HbA1c will be expressed as mean HbA1c values with standard deviations, and a two-sided *t* test will be used to compare HbA1c between placebo and prebiotic groups. Differences between the placebo and prebiotic groups’ C-peptide, inflammatory markers (IL-6, IFN-gamma, TNF-alpha, and IL-10), GLP-1, GLP-2 and intestinal permeability will be compared using a two-sided *t* test. Adverse events will be presented as the proportion of each event seen in each group (placebo and prebiotic). An intent-to-treat analysis will be used with the last data point carried forward for missing data. A secondary analysis will also be performed on a per-protocol basis with all subjects who have completed the intervention and are reported to be compliant with ≥80 % of the prebiotic or placebo packets consumed.

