## Discussion

DM1 in children is a chronic disease with the current mainstay of treatment being subcutaneous insulin administration multiple times a day, frequent capillary glucose monitoring and monitoring/counting carbohydrate intake at all meals and snacks. The management regimen in DM1 is invasive and labor intensive and may not always result in optimal glycemic control. Therefore, the addition of a simple, oral supplement such as a prebiotic to improve glycemic control would be very beneficial in this population.

Based on animal and human studies to date [9], we anticipate that a change in gut microbiota, gut permeability and inflammatory markers could occur over the course of several weeks of prebiotic supplementation. Hence, we anticipate that changes in these parameters will be detectable at the 3-month follow-up. The change in HbA1c will likely lag behind — as the life span of glycosylated red blood cells is 3 months, any improvement in glycemic control as a result of the 3-month prebiotic treatment may not be fully reflected at the 3-month follow-up, but may only become detectable at the 6-month follow-up. We will reassess all these parameters at 6 months to determine the persistence of effects and whether continued consumption of prebiotics is necessary to maintain the changes in gut microbiota, gut permeability and inflammatory markers observed.

Kellow et al. [9] published a systematic review on the metabolic benefits of prebiotics in human randomized controlled trials. Meta-analysis indicated a statistically significant effect of prebiotics on reduction in post-prandial glucose and post-prandial insulin levels. Conflicting results were seen in studies looking at fasting glucose, fasting insulin and HbA1c. No pediatric studies or populations with DM1 were identified for inclusion in this systematic review.

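### Carrying the last HbA1c forward enters baseline values as outcomes for early dropouts and end-of-treatment values at 6 months, and the stated 80% power belongs to a different analysis

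*Protocol article*

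**What the plan says.** The Analysis section fixes both the test and the missing-data rule. For the primary outcome, "a two-sided *t* test will be used to compare HbA1c between placebo and prebiotic groups"; no baseline adjustment is mentioned. For missing values, "An intent-to-treat analysis will be used with the last data point carried forward for missing data". The only other analysis named is a secondary per-protocol one, in children who completed the intervention and took at least 80% of the packets.

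On timing, "Blood will be collected at baseline, 3 months and 6 months for serum C-peptide, HbA1c", so nothing is measured between baseline and 3 months. The Background gives the objective as follows: "determine the effect of a 12-week dietary intervention with 8 g/day of prebiotic intake compared to placebo on glycemic control as measured by HbA1c". No primary visit is named. The Discussion says the HbA1c effect may not show fully until 6 months, and adds of that visit: "We will reassess all these parameters at 6 months to determine the persistence of effects".

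On size, the Internal pilot paragraph says "we will enroll 15 subjects per arm", assumes 20% dropout so that 12 per arm finish, and concludes that "we would be able to detect a mean difference in the absolute HbA1c of 1.5 between the placebo and prebiotic groups". The Full trial paragraph asks for 107 per arm for a difference of 0.5, raised to about 135 for the same dropout.

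**The concern.** A child who leaves before 3 months has only one HbA1c value, taken before treatment. Carrying it forward records no change for that child, whatever happened. A child who leaves between 3 and 6 months supplies an end-of-treatment value for a visit about three months after the product was stopped. That fills in by assumption the persistence that the 6-month visit is meant to measure.

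Three things are at stake. The estimate can be pulled towards no effect. If dropout differs by arm while HbA1c drifts, a difference can arise where none exists; unequal dropout is plausible, since the Intervention section anticipates gastrointestinal side effects. Finally, the sample size counts dropouts as absent and gives those who remain the full effect, whereas the analysis keeps them in with carried values. The pilot is also meant to supply proof-of-concept data for later trials, so a distorted estimate could carry over into their planning.

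**Working it through.** **Inputs from the Sample size section:** SD 1.3; differences 1.5 (pilot) and 0.5 (full trial); alpha 0.05; power 80%; dropout 20%; 15 enrolled and 12 completing, or about 135 and 107, per arm. The test is two-sided and allocation is 1:1. **Assumed, because the documents do not say:** when children leave, any HbA1c drift, the correlation between visits, and the share of the effect present at 3 months.

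**1. The plan's own figures reproduce.**
- Full trial: n = 2 × (1.960 + 0.842)² × 1.3² / 0.5² = 106.1, so 107 per arm. 107 / 0.8 = 133.75, so 134, in line with about 135.
- Pilot: detectable difference = 2.802 × 1.3 × √(2/12) = 1.49, in line with 1.5.
- These use the normal approximation. By the exact (noncentral) t, 107 per arm gives 80%, but 12 per arm gives 77% at 1.5 before any value is carried forward.

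**2. All 20% lost before 3 months, equally in both arms, no trend.** Expected difference = (1 − 0.20) × true difference.
- Full trial: 0.8 × 0.5 = 0.40. Power at 135 per arm is 71.2% (noncentral t) and 70.5% (simulation).
- Pilot: 0.8 × 1.5 = 1.2. Power at 15 per arm is 68.5% (noncentral t) and about 64% (simulation). The simulation is lower because it includes the extra spread from mixing treated and carried values in the prebiotic arm.
- Enrolment needed for 80% in the full trial: 2 × 2.802² × 1.3² / 0.40² = 165.8, so 166 per arm (167 by the noncentral t), not 135.

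**3. Early loss that the full trial can absorb.** With 135 per arm analysed, the detectable difference is 2.802 × 1.3 × √(2/135) = 0.443. Since 1 − 0.443/0.5 = 0.11, power falls below 80% once about 11% leave before 3 months.

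**4. Six-month comparison, full trial.** Let e be the share lost before 3 months, l the share lost between 3 and 6 months, and f the fraction of the 6-month effect already present at 3 months. Expected difference = 0.5 × (1 − e − l × (1 − f)).

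| e | l | f | Difference | Power (noncentral t, 135/arm) |
|---|---|---|---|---|
| 0.20 | 0 | any | 0.400 | 71% |
| 0.10 | 0.10 | 0.5 | 0.425 | 76% |
| 0.10 | 0.10 | 1 | 0.450 | 81% |
| 0 | 0.20 | 1 | 0.500 | 88% |

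Simulation agrees to within about a point: roughly 75 to 80% for the half-and-half rows and 89% for the last.

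**5. Under the null, with unequal dropout.** Assume HbA1c drifts up by 0.5 in both arms and 10% and 30% leave before 3 months. With carried values the arm means rise by 0.9 × 0.5 = 0.45 and 0.7 × 0.5 = 0.35, a spurious difference of 0.10. At 135 per arm the simulated type I error is about 9%; an analysis of completers stays near 5%.

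**6. Separating the two changes.** Simulated pilot power, difference 1.5, three children per arm lost before 3 months at random:

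| Assumed correlation | Carried forward, unadjusted | Carried forward, baseline-adjusted | Observed values, baseline-adjusted |
|---|---|---|---|
| 0.3 | 65% | 73% | 79% |
| 0.5 | 64% | 82% | 85% |
| 0.7 | 64% | 94% | 96% |

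Observed values without adjustment give the 77% of step 1. Starting from the planned analysis, most of the gain at the higher correlations comes from the baseline covariate.

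**The case against.** The strongest reply is that the loss of power depends on timing that the documents do not give. Dropout in the Internal pilot paragraph means not completing the study, and follow-up runs to 6 months, so some of the 20% may leave after 3 months. A reader might infer that power is well below 80% in any case. Steps 3 and 4 do not support that: it stays near or above 80% if early loss is below about 11%, or if losses are late and the effect is already present.

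A reader might also credit the whole rise from 64% to about 96% to abandoning carried-forward values. That is not supported either, because baseline adjustment accounts for most of it and the correlation of 0.7 is assumed. Nor is the whole pilot gap below 80% due to the missing-data rule, since about 3 points come from the normal approximation.

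It is fair to add that children who stop the product may truly gain nothing, in which case a treatment-policy effect is diluted under any method. The study is also framed as feasibility, about three children per arm would be imputed, and a per-protocol analysis is planned.

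These points limit the size and severity. They do not rescue the rule. The per-protocol set is selected on adherence, HbA1c is the stated primary objective, and the sample size makes no allowance for dilution from any source.

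**Conclusion.** The concern holds, conditionally in size. Carrying values forward is a poor primary rule for this visit schedule, and the 80% power was computed for completers at the full effect rather than for the planned analysis.

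If all 20% leave before 3 months, equally by arm and with no trend, power is about 71% for the full trial and 64 to 68% for the pilot, against 77% for 12 completers. For a 6-month comparison, full-trial power is about 75 to 80% if half leave late, with half to all of the effect present at 3 months, and about 89% if all leave late with the full effect present.

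The direction of bias is not fixed. It would be too strong to say that the rule always favours no effect at 3 months or always favours persistence at 6. Step 5 shows a false difference under one assumed pattern. For HbA1c itself the Discussion expects a lag, so a carried 3-month value could understate the 6-month effect.

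This should be fixed; it does not undermine the pilot as a feasibility study.

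**What to change.** - Make the primary analysis a likelihood-based repeated-measures model of the observed HbA1c values, adjusted for baseline, with visit and treatment-by-visit terms.
- Name one primary visit and take the treatment contrast there.
- Keep last observation carried forward at most as a labelled sensitivity analysis.
- Add one missing-not-at-random sensitivity analysis, for example placebo-based multiple imputation.
- State that the model's estimate is unbiased only if data are missing at random, and say whether the target is the effect regardless of stopping the product.
- Restate the power for the analysis actually planned, over a range of early and late dropout. Show the gain from baseline adjustment separately from the gain from dropping carried values, over a range of correlations (for the pilot, about 79%, 85% and 96% at 0.3, 0.5 and 0.7).

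The cost is a few sentences in the Analysis and Sample size sections. The software already named can fit the model, and no further data are needed.

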## Discussion

DM1 in children is a chronic disease with the current mainstay of treatment being subcutaneous insulin administration multiple times a day, frequent capillary glucose monitoring and monitoring/counting carbohydrate intake at all meals and snacks. The management regimen in DM1 is invasive and labor intensive and may not always result in optimal glycemic control. Therefore, the addition of a simple, oral supplement such as a prebiotic to improve glycemic control would be very beneficial in this population.

Based on animal and human studies to date [9], we anticipate that a change in gut microbiota, gut permeability and inflammatory markers could occur over the course of several weeks of prebiotic supplementation. Hence, we anticipate that changes in these parameters will be detectable at the 3-month follow-up. The change in HbA1c will likely lag behind — as the life span of glycosylated red blood cells is 3 months, any improvement in glycemic control as a result of the 3-month prebiotic treatment may not be fully reflected at the 3-month follow-up, but may only become detectable at the 6-month follow-up. We will reassess all these parameters at 6 months to determine the persistence of effects and whether continued consumption of prebiotics is necessary to maintain the changes in gut microbiota, gut permeability and inflammatory markers observed.

Kellow et al. [9] published a systematic review on the metabolic benefits of prebiotics in human randomized controlled trials. Meta-analysis indicated a statistically significant effect of prebiotics on reduction in post-prandial glucose and post-prandial insulin levels. Conflicting results were seen in studies looking at fasting glucose, fasting insulin and HbA1c. No pediatric studies or populations with DM1 were identified for inclusion in this systematic review.

Murri et al. showed that children with established DM1 have different gut microbiota from children without T1DM [6]. In addition to changes in the gut microbiota, altered gut permeability may also contribute to the pathogenesis of type 1 diabetes, as increased ‘gut leakiness’ has been shown in animal models preceding the development of diabetes [26]. It is hypothesized that the increased gut permeability allowed continued exposure to antigens that contribute to aspects of the immune dysregulation observed in DM1 [1]. Importantly, prebiotics have been shown to reduce gut permeability through a mechanism that involves GLP-2, a gut trophic factor [18]. In this current study, we aim to determine if treatment with prebiotics can decrease gut permeability, which will decrease endotoxemia and reduce insulin resistance. Improved insulin resistance may lead to improved glycemic control. In future studies, the role of prebiotics in altering disease progression in pre-diabetes will be examined.

This study will provide valuable information on whether the consumption of a prebiotic will alter gut microbiota and intestinal permeability in children with type 1 diabetes. This could potentially lead to improved glycemic control and adjunctive therapy that is inexpensive and easy to administer.

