### Intervention

Participants will be randomized to receive either placebo (maltodextrin 3.3 g orally/day; Agenamalt 20.222, Agrana Starch, Konstanz, Germany) or prebiotic (oligofructose-enriched inulin 8 g orally/day; Synergy1, Beneo, Mannheim, Germany). Inulin and oligofructose are approved as food ingredients in Canada and have been used previously in clinical trials [8, 25]. Both the prebiotic and placebo will be provided to participants in powder form in identical foil pre-weighed packets. Participants will be instructed to mix the packet with 250 mL of water until dissolved and to drink it 15–20 minutes prior to their evening meal. For the first 2 weeks, participants will be asked to only take half of the dose in order to minimize gastrointestinal side effects, and then they will take the full dose for the remaining 10 weeks.

Participants will be asked to record any diabetes-related or gastrointestinal adverse reactions, i.e. frequency of mild hypoglycemia (symptoms of hypoglycemia with a blood glucose less than 4 mmol/L and able to self-treat with oral rapid-acting carbohydrate), severe hypoglycemia (symptoms of hypoglycemia with a blood glucose less than 4 mmol/L but requires assistance with treatment due to decreased level of consciousness or has a seizure), diabetic ketoacidosis or flatulence. At the end of the 12 weeks, participants will be asked to return any remaining packets of placebo or prebiotic in order to assess for compliance. Telephone contact from a member of the research team will occur monthly to encourage compliance and recording of adverse reactions.

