### Data collection

Study visits will be coordinated with diabetes clinic visits; the data to be collected are outlined in Table 2. Demographic information will be collected at baseline. Anthropometric measures and assessment of insulin regimens, frequency of diabetic ketoacidosis (DKA) in previous 3 months, frequency of severe hypoglycemia in previous 3 months and average number of mild hypoglycemic episodes per week in the preceding 3 months will be assessed at baseline, 3 months and 6 months.

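### The primary HbA1c comparison names no visit, and the red-cell lifespan given cannot justify 6 months as the visit where the on-treatment effect appears

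*Protocol article*

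**What the plan says.** The primary objective appears at the end of the Background: "to determine the effect of a 12-week dietary intervention with 8 g/day of prebiotic intake compared to placebo on glycemic control as measured by HbA1c". It names no assessment time.

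Under Intervention, participants take half the dose for two weeks and "then they will take the full dose for the remaining 10 weeks". Dosing then stops: "At the end of the 12 weeks, participants will be asked to return any remaining packets of placebo or prebiotic".

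The section on glycemic control and inflammatory markers schedules blood for HbA1c at baseline, 3 months and 6 months, so there are two post-baseline values.

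The Analysis section says: "The primary outcome of HbA1c will be expressed as mean HbA1c values with standard deviations". The groups are compared with a two-sided t test, and significance is declared at p ≤ 0.05. Neither this section nor the two sample-size paragraphs (Internal pilot, Full trial) names a visit. Table 2 is not shown; its caption concerns procedures and data collection.

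The Discussion expects HbA1c to lag behind the other measures, "as the life span of glycosylated red blood cells is 3 months". It concludes that a glycaemic gain "may not be fully reflected at the 3-month follow-up, but may only become detectable at the 6-month follow-up". The next sentence gives the 6-month visit another purpose: "We will reassess all these parameters at 6 months to determine the persistence of effects".

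**The concern.** A condensed article that leaves the primary visit to the full protocol would not by itself be a fault. This article goes further. It names no visit in the places that define the primary test, and then prints a reason to prefer the later visit if the earlier one is null. A reader cannot tell which visit tests the primary hypothesis.

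The reason given also fails on the document's own figures. If red cells live 3 months and dosing ends at 12 weeks, the 3-month sample is the one that looks back over treatment.

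Three things are at stake:
- Two unranked visits, each tested at 0.05, offer two chances of a positive result.
- The two visits answer different questions: the effect while taking the product, and what remains or emerges afterwards.
- The Analysis section carries the last data point forward. If 6 months were primary, a missing value would be filled with the 3-month or baseline value, so the meaning of the imputed result depends on which visit is primary.

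The pilot is meant to inform a full trial of about 135 per arm, so an unsettled time point would carry into that design.

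**Working it through.** **1. The plan's own figures.** Full trial: n per arm = 2 × (1.960 + 0.842)² × 1.3² / 0.5² = 106.1, rounded up to 107, as stated. With 20% drop-out, 107 / 0.8 = 133.75, or 134, against approximately 135 stated. Pilot: (1.960 + 0.842) × 1.3 × √(2/12) = 1.49, against 1.5 stated. These reproduce, and none depends on a named visit.

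**2. What each sample looks back on.** Inputs: dosing from week 0 to week 12 (Intervention); lifespan 3 months (Discussion); samples at 3 and 6 months.

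| Sample | Period covered at a 3-month lifespan | Overlap with dosing |
|---|---|---|
| 3 months | months 0 to 3 | essentially all |
| 6 months | months 3 to 6 | none |

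**3. How much of an on-treatment effect each sample carries.** Assumptions, not in the document: lifespan L = 90 days, uniform cell ages, linear glycation, and an effect on glycaemia that ends with the last dose. The weight of glycaemia between a and b days before sampling is

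(1 − a/L)² − (1 − b/L)².

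- Sample on the last dosing day, constant effect from day 1 (a = 0, b = 84): 1 − (6/90)² = 0.996.
- Same, with half the effect during the two half-dose weeks: these weeks weigh (20/90)² − (6/90)² = 0.045; 0.996 − 0.045/2 = 0.973.
- Effect starting at week 4 (b = 56): 1 − (34/90)² = 0.857.
- Effect starting at week 6 (b = 42): 1 − (48/90)² = 0.716.
- Effect starting at week 8 (b = 28): 1 − (62/90)² = 0.525.
- Sample at 6 months, about day 182, which is 182 − 84 = 98 days after the last dose: 98 exceeds 90, so the weight is 0.

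Sensitivity with an assumed 120-day lifespan: last dosing day 1 − (36/120)² = 0.91; 6 months (22/120)² = 0.034. The contrast between the visits does not hinge on the exact lifespan.

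**4. Type I error if either visit may count.** With Z1 and Z2 the two test statistics, the error is 1 − P(|Z1| < 1.96, |Z2| < 1.96) under a bivariate normal. The correlation is assumed.

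| Correlation between visits | Type I error |
|---|---|
| 0 (upper bound) | 1 − 0.95² = 9.75% |
| 0.5 | 9.1% |
| 0.8 | 7.8% |
| 0.9 | 7.0% |

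**5. What a 6-month primary would mean for power.** Suppose the 0.5 effect persists at 6 months only in part (an assumption). With 107 per arm and SD 1.3, power is 80% at full persistence, 29% at half and 11% at a quarter.

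**The case against.** **A 6-month difference can be real.** The zero weight in step 3 assumes that the glycaemic effect ends with dosing. The Discussion proposes a downstream chain from permeability through endotoxemia and insulin resistance to glycaemic control, and treats carry-over as an open question. A reader might infer that the 6-month value cannot measure any effect of the intervention. The document does not support that: a randomized difference at 6 months is a valid effect of assignment to 12 weeks of product, of a persisting or delayed kind. This part of the objection stands.

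**Incomplete capture at 3 months is reasonable.** With the half-dose start and a slow onset, the share captured falls from nearly all to 86% at a week-4 start and 53% at a week-8 start. This stands too. The fault lies only in the claim that red-cell turnover could make the effect detectable solely at 6 months.

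**One visit can serve two purposes.** A delayed and a persisting effect can both be looked for at 6 months, so the two uses are not strictly incompatible. What remains is that neither is the on-treatment effect for which red-cell turnover is offered as the explanation.

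**The error rate is conditional.** No section says that either visit may count as success. The 7.8% to 9.1% shows the cost of leaving the choice open and is not the error rate of a stated rule.

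**Visit timing.** A reader might infer from "Study visits will be coordinated with diabetes clinic visits" that the 3-month samples could fall well after the last packet. The text does not show this. Coordination can simply mean booking the visits together, the Discussion itself calls the treatment 3 months long, and visit windows are detail that an article leaves to the full protocol.

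**It is a pilot.** With 15 per arm and a detectable difference of 1.5, its HbA1c test is unlikely to be decisive at either visit. That lowers the urgency, but the article still makes HbA1c the primary objective.

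**Conclusion.** The point holds in limited form. No section shown fixes the visit for the primary HbA1c test, and the Discussion points to 6 months with a rationale that its own 3-month lifespan and the 12-week dosing period contradict. At that lifespan the 3-month HbA1c covers treatment and the 6-month HbA1c covers only the time afterwards. Red-cell turnover therefore cannot make 6 months the visit where the on-treatment effect appears.

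The possible inflation of type I error is to about 7.8% to 9.1%. This applies only if either visit may be claimed, and only for an assumed correlation of 0.8 to 0.5. The shares captured at each visit rest on uniform cell ages and linear glycation; the finding of no overlap at 6 months rests only on the document's own lifespan and dosing period.

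This should be fixed, but it does not undermine the pilot. The stated sample sizes are unaffected.

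**What to change.** 1. In the Analysis section, and before unblinding, state that the single primary endpoint is HbA1c at the end of the 12-week treatment, that is, at the 3-month visit. Repeat the visit in the primary objective.
2. Label the 6-month HbA1c a secondary endpoint for a persisting or delayed effect.
3. Reword the Discussion sentence to match: the effect may be incompletely captured at 3 months because of the half-dose start and slow onset, and a 6-month difference would reflect glycaemia after dosing ended.

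The cost is a few sentences. Sample size, product and visit schedule do not change. The Trial status section says that recruitment had only just begun, so the choice could be recorded before outcomes were known.
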